#### Supplemental Analyses

Supplemental analyses will build on the primary analytic models to further explore the intervention’s impact. (1) Dose-response effects: To assess potential dose-response relationships, digital app metadata will be incorporated into the analytic models. Specifically, fixed effects for the number of intervention sessions completed will be added to examine whether greater engagement is associated with greater reductions in suicidal ideation and depressive distress. (2) Heterogeneity of treatment effects: We will examine whether intervention effects vary across subgroups defined by race and ethnicity, gender identity, and geographic region. This will be done by including interaction terms between intervention arm assignment and each subgroup variable in the primary model [61]. Significant interactions will be graphed and interpreted to identify whether certain groups derive greater benefit, which can inform future targeted dissemination and scale-up efforts. (3) Sustained intervention effects: To evaluate whether intervention effects are maintained over time, we will analyze data from participants in the immediate arm who completed both the month 6 and the month 12 assessments. The model will estimate the marginal effect of time on past 3-month suicidal ideation between months 6 and 12. The analytic model will include a common intercept, a fixed effect for time (month 6 vs month 12), and relevant covariates. The risk ratio will be calculated as the exponential of the time coefficient.

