## Introduction

### Background

Transgender, nonbinary, and gender diverse (TGD) individuals experience multiple forms of interpersonal and structural stigma and face intersectional gender-, race-, and socioeconomic-based minority stress at various levels [1-4], including within their own families [5-8], resulting in life-threatening health disparities. Suicide, one of the top 10 causes of death in the United States and the second leading cause of death among young adults [9,10], is 2-4 times more likely to affect TGD young adults compared to their cisgender peers [11,12]. Rates of depressive distress are similarly elevated among TGD young adults [11-13], as are other mental health conditions such as nonsuicidal self-injury, anxiety, and substance use [11-14].

Compounding these disparities, TGD individuals are more likely than the general population to identify as Black or Hispanic, and they frequently experience race-based health inequities [15]. For Black and Hispanic communities, which already face a disproportionately high burden of suicide compared to the general population [16], these intersecting vulnerabilities further increase risk for Black and Hispanic TGD individuals.

There is an urgent need for evidence-based interventions that address the unique mental health challenges faced by TGD young adults. Research shows that family functioning and support—including communication, satisfaction, and acceptance—are protective factors for TGD individuals’ mental health [5,6,17,18]. Additionally, a strong sense of community connectedness is associated with improved mental health outcomes [19-21]. These findings emphasize the crucial role of supportive relational contexts—within families and communities—in promoting TGD individuals’ well-being. Self-guided digital mental health interventions, including web- and smartphone-based apps, have demonstrated effectiveness in reducing depression and suicidality among young people [22,23]. They have also been shown to increase perceived social support [24] and are generally well-accepted by individuals experiencing mental health concerns [25]. However, to our knowledge, no evidence-based digital app intervention currently exists that is designed to reduce depression and suicidality among TGD young adults, while also engaging their caregivers or families in the process.

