### Statistical Analysis

#### Power

The study aims to enroll 500 TGD participants between the ages of 18 and 24 years, 125 caregivers, and one-quarter of the young adult sample in a TGD young adult-caregiver dyad. The primary outcome of interest is past 3-month suicidal ideation.

Power calculations determined the sample size needed to detect a significant difference in suicidal ideation between the immediate and deferred intervention arms. To detect an effect size of at least 30% (risk ratio=0.70) in the reduction of suicidal ideation from baseline to 6 months postrandomization, a total sample size of 400 participants (200 per arm) is required to achieve 80% power at a 0.05 significance level.

We selected a 30% effect size threshold based on the assumption that smaller differences would not be clinically meaningful for public health scale-up. To account for an estimated 20% attrition rate, we plan to enroll 500 TGD young adult participants and 125 caregivers at baseline, yielding an anticipated analyzable sample of 400 TGD young adult participants and 100 caregivers.

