#### Primary Aim Analyses

The primary outcome is suicidal ideation in the past 3 months, assessed using the 6-item C-SSRS. The C-SSRS demonstrates strong validity, with 100% sensitivity and 99.4% specificity for identifying aborted suicide attempts, and 100% sensitivity and specificity for classifying interrupted and actual suicide attempts, when compared to clinician-administered instruments [41]. The secondary outcome is depressive distress over the past 2 weeks, measured using the Patient Health Questionnaire-9, where a score of ≥10 indicates a positive screen for symptoms of clinically elevated depressive symptoms (88% sensitivity and 88% specificity for detecting major depression) [43].

Before analysis, data will be audited for quality and completeness. Descriptive statistics—including counts, percentages, means, medians, standard deviations, and ranges—will summarize baseline characteristics. Group differences at baseline will be assessed using *t* tests for continuous variables and chi-square tests for categorical variables. Variables that differ significantly between study arms may be included as covariates in subsequent models. All analyses will be conducted using SAS or R statistical software.

To evaluate intervention effectiveness, we will use an intention-to-treat approach. Poisson generalized estimating equations with a log link function will estimate the population-average (marginal) effect of the intervention on suicidal ideation from baseline to 6 months postrandomization [60]. An unstructured correlation structure will be used to account for within-subject correlations across repeated measures (baseline, 3 months, and 6 months).

The primary endpoint analysis will compare the proportion of participants reporting suicidal ideation in the past 3 months between the immediate and deferred (waitlist control) arms. The model will include a common intercept and fixed effects for the intervention arm (immediate vs deferred) and time point (3 vs 6 months). Baseline characteristics that differ significantly between groups and variables related to missingness will be included as covariates, if appropriate.

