The primary estimate is the intervention arm assignment. The risk ratio will be estimated by exponentiating the intervention coefficient from the model. Wald tests with robust standard errors will be used to construct 95% CIs and test the primary hypothesis. For TGD young adult-caregiver dyads, we will adjust models to account for dyadic interdependence.

The same analytic approach will be applied to the secondary outcome of past 2-week depressive distress. Statistical significance will be determined at the 0.05 level.

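### Subgroup benefit is judged, as stated, from risk-ratio interactions alone; absolute risks and risk differences by subgroup should be reported beside them

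*Protocol article*

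**What the plan says.** Under Primary Aim Analyses, "Poisson generalized estimating equations with a log link function will estimate the population-average (marginal) effect" of the intervention on suicidal ideation, and "The risk ratio will be estimated by exponentiating the intervention coefficient from the model". Under Supplemental Analyses, item 2, effects are compared across "subgroups defined by race and ethnicity, gender identity, and geographic region" by "including interaction terms between intervention arm assignment and each subgroup variable in the primary model". The use of the result is also fixed there: "Significant interactions will be graphed and interpreted to identify whether certain groups derive greater benefit, which can inform future targeted dissemination and scale-up efforts".

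The statistical sections name no risk difference, additive interaction or arm-specific risk by subgroup. They do not give the scale of the graphs. The Background section expects unequal risk on one of the three subgroup variables: after describing the suicide burden in Black and Hispanic communities, it says that "these intersecting vulnerabilities further increase risk for Black and Hispanic TGD individuals". It gives no subgroup rates of ideation.

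**The concern.** An arm-by-subgroup term in a log-link model is a log ratio of risk ratios. It asks whether the proportional reduction in ideation differs between groups. A reader planning dissemination will usually also want to know how many cases of ideation are prevented per 100 people reached, and that depends on the group's untreated risk as well as on its risk ratio. When untreated risk differs, equal risk ratios give unequal absolute benefit, and equal absolute benefit gives unequal risk ratios.

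As written, a significant ratio interaction is the only stated route to a statement about greater benefit. A real difference in cases prevented can therefore go unreported, and now and then a group can be named as benefiting more although fewer cases are prevented in it. Larger subgroups or a multiplicity correction would not change this, because it is a matter of scale.

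**Working it through.** **Inputs from the article.** Log-link model and risk ratio (Primary Aim Analyses). Design risk ratio 0.70, 400 analysable participants at 200 per arm, 80% power, 0.05 level, 20% attrition (Power).

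**Assumptions.** Control-arm ideation is not stated, overall or by subgroup. I take two subgroups of equal size, hence 100 per arm per subgroup, two-sided 0.05, and one binary outcome per person instead of the repeated-measures model. Control risks are 60% (group A) and 30% (group B), with 50% and 40% as a milder case.

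**The article's own figure.** Without a control rate, 400 cannot be reproduced from the stated inputs alone. The usual two-proportion formula at a risk ratio of 0.70 gives 203 per arm at an assumed control rate of 45% and 196 at 46%, against 244 at 40% and 170 at 50%. Attrition is exact: 400/0.8 = 500. Both assumed pairs average 45%, so they are compatible with the sample size.

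**Formulas.** Points prevented = control risk × (1 − RR). For the interaction on the log-RR scale, SE² = Σ (1 − p)/(100p) over the four arm-by-subgroup cells; on the risk-difference scale, SE² = Σ p(1 − p)/100. The rejection rates below come from 200,000 simulated trials per case; normal approximations are given for comparison.

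**Case (a): common RR 0.70, risks 60% and 30%.**
- A: 0.60 × 0.30 = 18 points, NNT 5.6. B: 0.30 × 0.30 = 9 points, NNT 11.1.
- The ratio of risk ratios is 1, so the interaction is null by construction. The ratio term is significant in 4.8% of trials, which is its false-positive rate.
- Additive interaction test: significant in 17% (normal approximation 16%).

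**Case (b): equal benefit of 12 points.**
- A: 60% to 48%, RR 0.80. B: 30% to 18%, RR 0.60.
- The ratio term is significant in 15.3% (approximation 16.5%), and 99% of those results name B. The risk ratios do differ here, so this is power to detect a real ratio difference. It becomes misleading only if read as a difference in cases prevented.

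**Case (c): A gains more in absolute terms.**
- A: 60% to 44%, 16 points, RR 0.733. B: 30% to 18%, 12 points, RR 0.600.
- Log-ratio difference: ln(0.733/0.600) = 0.201. SE² = 0.00667 + 0.01273 + 0.02333 + 0.04556 = 0.0883, so SE = 0.297 and z = 0.68. Power is about 10.4% by approximation and 9.4% by simulation.
- 96% of the significant results name B, so B is named in about 0.96 × 9.4% = 9% of all trials.
- Additive interaction test: significant in about 8%.

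**Milder gap: 50% against 40%.**
- Common RR 0.70: 15 against 12 points.
- Equal 12-point benefit: RRs 0.76 and 0.70. The ratio term is significant in 5.9%, against a nominal 5%.

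**The case against.** The strongest reply is that the ratio scale is the article's own. The Power section defines the effect worth scaling up as an "effect size of at least 30% (risk ratio=0.70"), and the primary estimate is a risk ratio. Testing heterogeneity in that same model is consistent and is not an error. This stands.

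Second, the absence of an absolute measure is partly silence. The graphs might show arm-specific risks, and an analysis plan might add risk differences. This stands in part: the article does state both the method and its use, and only significant ratio interactions are to be graphed, so case (a) would normally not reach a graph.

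Third, a reader might infer that the plan would steer dissemination away from the highest-risk groups. The article does not support that. A null ratio interaction leads to no targeting at all. Misdirection needs a significant reversal, which occurs in about 9% of trials in case (c). It also needs the lower-risk group to have the lower risk ratio; if the higher-risk group has the lower risk ratio, both scales agree.

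Fourth, the 60% against 30% gap is an assumption, and the Background statement is qualitative, concerns race and ethnicity, and says nothing about gender identity or region. This stands, and the milder case shows how quickly the effect fades.

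Finally, the additive test is weak too, so replacing one significance test with another would gain little. That also stands, and it shapes the remedy.

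**Conclusion.** The point holds in a limited form. The stated rule reads significance on the risk-ratio scale as showing who benefits more, and on that scale alone a difference in absolute benefit can be missed and the ranking can sometimes differ from cases prevented. With assumed control risks of 60% and 30%, a twofold difference in points prevented (18 against 9) leaves the ratio interaction null. With 16 against 12 points, about 9% of trials would give a significant term, nearly all naming the lower-risk group. At 50% and 40% little distortion remains. All these sizes rest on assumed risks, equal subgroups of 100 per arm and a single-time-point approximation; finer race and ethnicity categories would be smaller and noisier.

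The ratio test should stay, and the documents do not support a rule that targeting must rest on absolute effects only. Severity is minor: the analysis is supplemental, its results only may inform later dissemination, and the primary test and sample size are untouched.

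**What to change.** Under Supplemental Analyses, item 2, keep the ratio interaction and add the following.

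- For every subgroup, whether or not the ratio interaction is significant, report the model-standardized risk in each arm, the risk difference and the risk ratio with 95% CIs, all from the same fitted GEE.
- Show the between-subgroup difference in risk differences with its 95% CI beside the ratio of risk ratios.
- State that no conclusion about greater benefit or targeting will rest on ratio-scale significance alone, and that these results are exploratory.

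The cost is a few lines of wording, a little code on the same model and one extra table. The intervals will be wide: at 100 per arm, the SE of a subgroup risk difference is about 7 points (60% against 44%: √(0.60 × 0.40/100 + 0.44 × 0.56/100) = 0.070). Power on the additive scale is low, about 17% in case (a) and 8% in case (c). The gain therefore lies in showing both scales with their uncertainty.

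### The subgroup plan lets statistical significance decide which interactions are graphed, interpreted and used to inform targeting, without calling the results hypothesis-generating (minor)

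*Protocol article*

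**What the plan says.** Item 2 of Supplemental Analyses in the Protocol article names three effect modifiers in advance: "We will examine whether intervention effects vary across subgroups defined by race and ethnicity, gender identity, and geographic region". The method is an interaction test: "This will be done by including interaction terms between intervention arm assignment and each subgroup variable in the primary model". The article then says what follows from a significant result: "Significant interactions will be graphed and interpreted to identify whether certain groups derive greater benefit, which can inform future targeted dissemination and scale-up efforts".

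Three other places bear on how to read this:

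- **Status.** The section opens with "Supplemental analyses will build on the primary analytic models to further explore", so the analysis is labelled supplemental and exploratory.
- **Level.** The article's only general rule closes Primary Aim Analyses: "Statistical significance will be determined at the 0.05 level". It is not repeated for the interaction terms, and no other level appears.
- **Sizing.** Under Power, for the overall comparison (risk ratio 0.70), "a total sample size of 400 participants (200 per arm) is required to achieve 80% power at a 0.05 significance level". Nothing is sized for an interaction.

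**The concern.** The sentence on significant interactions fixes three things at once: the trigger (significance), the statement it permits (which groups gain more) and the use of that statement (targeted dissemination and scale-up). With three modifiers tested in one trial, the chance that at least one crosses 0.05 by luck is well above 5%.

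A trial sized for its main effect also has little power for interactions. A moderate real difference will therefore usually be missed, and the estimates that do reach significance will tend to be too large. Filtering the display by significance compounds this, because the reader is promised the extreme contrasts and nothing is said about the rest.

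The practical stake is that a chance difference by race, gender identity or region could shape who is offered the app later. The trial sets a recruitment goal of at least 50% people of color, so a misleading statement about who benefits could work against a group it means to serve.

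**Working it through.** **The plan's own figure.** The article states no error rate for the interactions; its one related figure is the sample size. "To account for an estimated 20% attrition rate, we plan to enroll 500 TGD young adult participants and 125 caregivers at baseline": 500 × (1 − 0.20) = 400, or 200 per arm, which agrees with Power. The 200 per arm cannot be checked fully because no control-arm ideation risk is given. A two-sided 0.05 test of risk ratio 0.70 with 80% power needs 203 per arm at a control risk of 0.45, so the figure fits a risk of about that size. This concerns the overall effect only.

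**Inputs for the subgroup error rate**

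- Modifiers: 3 (Supplemental Analyses, item 2).
- Level: 0.05 (Primary Aim Analyses). That it also applies to the interactions is an inference, since no other level is given.
- Assumed: no true heterogeneity, one joint test per modifier, and tests roughly independent of one another.

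**One outcome (suicidal ideation)**

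P(at least one significant) = 1 − (1 − 0.05)³ = 1 − 0.8574 = 0.143.

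Without the independence assumption, the value lies between 5% (three tests that always agree) and 3 × 0.05 = 15% (the Bonferroni bound). Correlation between modifiers, for example race and region, would pull it somewhat below 14.3%.

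**If depressive distress is also tested (not stated outright)**

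Six independent tests give 1 − 0.95⁶ = 0.265. For three independent interactions, each on two correlated outcomes:

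| Correlation between outcome test statistics | P(at least one significant) |
|---|---|
| 0 | 26.5% |
| 0.5 | 24.8% |
| 0.7 | 23.0% |
| 0.9 | 19.7% |
| 1 | 14.3% |

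**If single coefficients were tested instead of one joint test**

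The article does not say which is meant, and the number of levels per modifier is not fixed. In a simulation for one outcome, with contrasts that share a reference level correlated at 0.5, the rate is about 25% with 2 terms per modifier and about 33% with 4, 2 and 3 terms. Both sets of term counts are assumptions.

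**Interaction power (illustration only)**

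Assume 200 per arm, a modifier that splits the sample 50/50 (100 per cell), and true risk ratios of 0.60 and 0.80. The variance of the log ratio of risk ratios is the sum of (1 − p)/(np) over the four cells. At an assumed control risk of 0.46 the cell risks are 0.46, 0.46, 0.276 and 0.368:

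- Variance = 0.54/46 + 0.54/46 + 0.724/27.6 + 0.632/36.8 = 0.0669, so SE = 0.259.
- z = ln(0.80/0.60)/0.259 = 0.288/0.259 = 1.11.
- Two-sided power at 0.05 is about 20%.

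Over control risks of 0.20, 0.30, 0.40 and 0.50, the same formula gives 10%, 13%, 17% and 22%. Power is low throughout that range.

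**The case against.** The case for leaving the text alone has weight. The section is supplemental and says it explores. The modifiers are few and prespecified, and they are tested by interaction terms rather than by separate p-values within subgroups. The results only may inform later efforts; no decision within the trial rests on them. Unadjusted exploratory interaction tests are common practice, and multiplicity rules and display details usually sit in a statistical analysis plan, which is not shown here. All of that stands. The lack of an adjustment is therefore not itself an error, and the point is minor.

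A reader might also infer more than the text supports:

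- **That both outcomes are tested for interaction, giving a risk near 25%.** Primary Aim Analyses does say "The same analytic approach will be applied to the secondary outcome of past 2-week depressive distress", and the lead-in to Supplemental Analyses uses the plural for models. But item 2 refers to the primary model in the singular, and unlike item 1 it does not name depressive distress. A figure of 25% also needs an assumed correlation of about 0.5 between outcomes.
- **That non-significant interactions will be withheld.** The text does not say so; it is silent on them.
- **That significant interactions will decide who receives the app.** The wording is weaker than that.
- **That low interaction power is a flaw of this trial.** It is usual in trials sized for a main effect, and the percentages above depend on an assumed control risk. Low power is a reason for cautious wording.

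The objection does not remove the stated trigger. Even if a separate plan adds an adjustment, this sentence still makes significance the gateway to a statement about who benefits and names dissemination as its use. Nowhere does the item call such a finding hypothesis-generating.

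**Conclusion.** The concern holds in a limited form and is minor. As written, significance is the trigger for graphing and interpreting a subgroup interaction, for saying which groups benefit more and for informing targeted dissemination. With no true heterogeneity, the chance of at least one false differential-benefit statement on suicidal ideation is about 14%. That rests on the 0.05 level applying to the interactions, one joint test per modifier, and roughly independent tests. It is a familywise rate under a complete null: each single test still errs 5% of the time, and the figure is not an unconditional chance of a false claim. The rate rises if depressive distress is included or if single coefficients are tested, but the article commits to neither. No confirmatory conclusion is affected.

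**What to change.** Replace the sentence on significant interactions with wording such as:

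> For each modifier, one joint arm-by-subgroup test will be reported, and arm risk ratios with 95% CIs will be shown for every level of all three modifiers whether or not the interaction is significant. These analyses are exploratory; any apparent difference is hypothesis-generating and will not by itself be used to target dissemination.

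It would also help to state whether item 2 covers depressive distress.

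The cost is one extra forest plot and a more cautious subgroup statement, with no added participants or data. A Holm adjustment over the three tests is optional. Its first step would be 0.05/3 = 0.0167, and Bonferroni at that level holds the familywise rate at 1 − (1 − 0.0167)³ = 4.9%, but it would lower power that is already low. Full display with an exploratory label deals with the selective display and the overclaiming without that loss.

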**Figure 1 figure1:**
[figure not shown]
TransHealthGUIDE (Transforming Mental Health for Transgender and Gender-Diverse Young Adults Using Interventions to Drive Equity) study schema. Target sample size is 500 TGD young adults, with one-quarter (125 participants) in a dyad with a caregiver (target sample size of 125 caregivers). TGD: transgender, nonbinary, and gender diverse.

Participants in the immediate intervention arm receive full access to the TransHealthGUIDE digital app for the first 6 months. This is followed by a 6-month observation period during which they retain access to the app but receive no new intervention content or engagement prompts. Participants in the deferred intervention arm receive limited access to the app for the first 6 months, consisting primarily of curated local, regional, and national support resources. At the 6-month mark, participants in the deferred arm are granted full access to the digital app for the remainder of their participation.

Survey assessments are administered at baseline, 6 months, and 12 months to evaluate primary outcomes (past 3-month suicidal ideation and past 2-week depressive distress) as well as secondary measures.

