#### Attrition Analysis

Attrition will be monitored monthly using data visualization techniques to track trends over time. Key metrics will include total enrollment, representation of target subgroups (by race, ethnicity, and geographic region), and rates of loss to follow-up. Statistical analyses will be conducted to compare participants retained in the study versus those lost to follow-up, focusing on differences in baseline characteristics.

Patterns of missingness will be systematically examined, and baseline responses will be compared between participants with complete versus incomplete data. To address potential biases due to missing data, modern missing data techniques will be used, with an emphasis on multiple imputation methods [65]. Sensitivity analyses will be conducted to compare results from complete-case analyses with those using multiple imputation, allowing for an assessment of the potential bias introduced by missing data.

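### The sustained-effect analysis gives the change in ideation among immediate-arm participants who completed both month 6 and month 12; it does not show whether the intervention effect is maintained

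*Protocol article*

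**What the plan says.** Item 3 of Supplemental Analyses in the protocol article asks whether the intervention's effects persist. For this, "we will analyze data from participants in the immediate arm who completed both the month 6 and the month 12 assessments". The target quantity is given directly: "The model will estimate the marginal effect of time on past 3-month suicidal ideation between months 6 and 12". So is the model: "The analytic model will include a common intercept, a fixed effect for time (month 6 vs month 12), and relevant covariates". The reported risk ratio is the exponential of the time coefficient. There is no arm term and no baseline time point.

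Three other places bear on this:

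- Study Design, on the deferred arm: "At the 6-month mark, participants in the deferred arm are granted full access to the digital app for the remainder of their participation".
- Attrition Analysis, on missing data in general: "modern missing data techniques will be used, with an emphasis on multiple imputation methods". It adds a sensitivity comparison of complete-case and imputed results.
- Power covers only the between-arm comparison to month 6: for a risk ratio of 0.70, "a total sample size of 400 participants (200 per arm) is required to achieve 80% power at a 0.05 significance level". No sample size or power is given for the sustained-effect analysis.

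**The concern.** The stated aim and the quantity estimated differ. The aim concerns an intervention effect, which is a contrast between having and not having the intervention. The model returns a before-and-after ratio in one arm. Three things can then pull that ratio away from the answer sought.

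- **Selection.** Someone in the immediate arm who misses either survey is outside the analysis set by definition, so imputation has nobody to act on. If people whose ideation returns are the ones who stop responding, the ratio moves toward 1.
- **Background change.** Ideation may rise or fall between months 6 and 12 for reasons unrelated to the app. A one-arm time coefficient absorbs all of it.
- **Precision.** The trial was sized for a different contrast, so a partial loss of benefit may go undetected.

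At stake is how a supplemental durability result can be described. The between-arm comparison at 6 months is not touched.

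**Working it through.** **The plan's own figure.** The control-arm risk is not stated, so 200 per arm cannot be reproduced from the document alone. I solved for it with the pooled-variance formula, two-sided 0.05:

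n per arm = [1.96·√(2p̄(1−p̄)) + 0.842·√(p₁(1−p₁) + p₂(1−p₂))]² / (p₁−p₂)²

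With p₁ = 0.45 and p₂ = 0.70 × 0.45 = 0.315, p̄ = 0.3825 and n = (1.347 + 0.573)² / 0.135² ≈ 203. Exactly 200 per arm gives 80% power at p₁ ≈ 0.453, so p₂ ≈ 0.317. Other variants imply 0.463 (log risk ratio Wald), 0.474 (continuity-corrected) or 0.389 (one-sided). The attrition step reproduces: 400 / (1 − 0.20) = 500.

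**Assumptions from here on.** Control risk 0.453, with 0.30 as a lower alternative. Month-6 immediate-arm risk p₆ = 0.317. Both-visit completers n = 200, or 200 × 0.8 = 160 after a further 20% loss. Within-person correlation ρ = 0.3 to 0.7. None of these is in the document except the 200 per arm and the 20%.

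**Selection.** Suppose the benefit is wholly lost, so p₁₂ = 0.453 and the true ratio is 0.453 / 0.317 = 1.43. Take ρ = 0.5. Then P(ideation at both visits) = 0.317 × 0.453 + 0.5·√(0.317·0.683·0.453·0.547) = 0.259, and P(month 6 only) = 0.317 − 0.259 = 0.058.

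- Loss of 40% among those with ideation at month 12 and 5% among others. Retained: 0.453 × 0.60 + 0.547 × 0.95 = 0.791. Observed p₁₂ = 0.272 / 0.791 = 0.344. Observed p₆ = (0.259 × 0.60 + 0.058 × 0.95) / 0.791 = 0.266. Ratio 1.29; power, starting from 250 in the arm, 65%.
- Loss of 20% against 5%: retained 0.882, ratio 0.411 / 0.297 = 1.38, power 93%.
- Equal loss in both groups leaves 1.43.

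**Background change.** If untreated ideation at month 12 is f times its month-6 level, the within-arm ratio is f when the benefit is fully kept and f / 0.70 when it is wholly lost.

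| f | Benefit fully kept | Benefit wholly lost |
|---|---|---|
| 1.0 | 1.00 | 1.43 |
| 0.9 | 0.90 | 1.29 |
| 0.8 | 0.80 | 1.14 |
| 0.7 | 0.70 | 1.00 |

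A ratio of 1.00 thus fits full maintenance with no background change, and also total loss with a 30% background fall.

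**Power of the time test.** Var(log RR) = [(1−p₆)/p₆ + (1−p₁₂)/p₁₂ − 2ρ·√(p₆(1−p₆)p₁₂(1−p₁₂)) / (p₆p₁₂)] / n.

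Example: half the benefit lost, p₁₂ = 0.317 + 0.5 × 0.136 = 0.385, ratio 1.21, n = 200, ρ = 0.5. Variance = (2.155 + 1.597 − 1.855) / 200 = 0.0095, SE = 0.097, power = Φ(0.194/0.097 − 1.96) ≈ 51%. Across the ranges, with no selection and no background change:

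| Loss of benefit | n = 200, control 0.453 | n = 160, control 0.453 | n = 200, control 0.30 | n = 160, control 0.30 |
|---|---|---|---|---|
| Complete (1.43) | 90-99.8% | 83-99% | 68-95% | 58-90% |
| Half (1.21) | 39-72% | 33-63% | 24-49% | 20-41% |
| One quarter (1.11) | 14-26% | 12-22% | 10-17% | 8-14% |

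**The case against.** The defence has several good points.

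- **Missing data are already addressed.** Attrition Analysis plans imputation, a comparison of retained and lost participants, and a complete-case comparison, and it does not limit these to the primary outcome. That intention stands. But item 3 defines its set by completion of both surveys, so followed literally the imputation cannot reach it. The two passages need to be reconciled.
- **The lack of an untreated month-12 group is a consequence of the waitlist design.** This stands in full. It is not an oversight in the analysis, and no refit cures it; only the description of the result can change.
- **Weak power for partial waning is ordinary in a supplemental analysis.** This also stands, and every driver of the power figures is assumed.

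A reader might also infer more than the document supports:

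- That a non-significant time coefficient will be declared maintenance. No passage states such a rule, and interpretation rules may sit in an analysis plan not shown here.
- That scale-up depends on durability. Power ties scale-up to the 30% effect threshold, and Limitations makes wider dissemination depend on demonstrated effectiveness. Neither mentions month 12.
- That the completer set breaches intention-to-treat. Under Primary Aim Analyses, "we will use an intention-to-treat approach" refers to evaluating effectiveness in the randomised comparison to 6 months; a labelled within-arm analysis does not break it.

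**Conclusion.** The concern holds in a limited form. As written, item 3 estimates the change in prevalence of ideation from month 6 to month 12 among immediate-arm completers, which is not the maintenance of an intervention effect that it sets out to evaluate.

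The absence of a contrast is the most serious part: an assumed 30% background fall would hide a complete loss of benefit. Selective dropout pushes the ratio toward 1, but in the ranges tried it moves a wholly lost benefit only from 1.43 to 1.38-1.29, so dropout alone does not create apparent maintenance. Low power applies to partial loss (33-72% for half the benefit at a control risk near 45%). It would be wrong to say that low power would generally hide a complete loss: at that control risk, power is 83% or more without selection or background decline, although it is 58-95% if the control risk is 30%.

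These sizes rest on assumed control risk, within-person correlation, month-12 numbers, dropout pattern and background trend. The primary conclusion does not depend on this analysis.

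**What to change.** In item 3 of Supplemental Analyses:

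1. Analyse everyone randomised to the immediate arm, using the multiple imputation already planned under Attrition Analysis. Keep the both-visit completers as a sensitivity analysis.
2. Put baseline, month 6 and month 12 in the model, and report month 12 versus month 6 and month 12 versus baseline, each with a 95% CI.
3. Describe the result as a within-arm change over time, not as evidence that the between-arm effect is maintained.

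The cost is wording and one refit with data and methods already planned. The downside is a weaker durability statement. Two limits remain. Imputation reduces selection bias but may not remove it if dropout depends on unobserved month-12 ideation. The baseline contrast is still within one arm, so background change and regression to the mean stay mixed with any effect.
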